***Intervention Group:***

The intervention will start in the NICU and continue for up to 12-months corrected age. It is divided into 3 blocks:

- **Block A** is defined as the period from enrollment until discharge from the NICU.
- **Block B** is defined as post-NICU until 3-months corrected age.
- **Block C** is defined as 3-months until 12-months corrected age.

All intervention sessions within each of the blocks will focus on providing a high dosage of intervention while incorporating a strengths-based approach that focuses on the principles of active learning, environmental enrichment, and caregiver engagement. Infants in the intervention group may also receive services as assigned by their managing care providers, including referral to Early Intervention or outpatient therapy services. Participants will not be prevented from receiving any service that they would otherwise be eligible for as a result of participation in this study. Study staff will monitor the frequency and type of additional services received using parent surveys. We will provide participants with contact information for study staff.

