***Assessment Timeline:*** Assessments will be completed at study enrollment and thereafter at monthly intervals up to 3 months corrected age, then at 3-months corrected age, 6-months corrected age, 9-months corrected age, 12-months corrected age, 18-months corrected age (optional), and 24-months corrected age (optional). The number of assessments prior to 3 months corrected age will vary by preterm status and age of enrollment. Optional assessments will be completed if (i) the study is still ongoing and (ii) the caregiver agrees to do so. If infants are unable to complete any required assessment sessions, an attempt to re-schedule will be made. If infants are unable to complete a testing session, their participation in the study will not be affected; however, the study team will appropriately document the missing data.

***Additional monitoring:*** Intervention therapists and study team members will monitor infant response to intervention sessions, caregiver engagement (caregiver- and therapist-report) compliance to key principles, percentage of intervention sessions completed, the dosage of Activity Playbook activities achieved (caregiver report), any adverse events/changes in medical status, additional services received outside of study participation, general medical and health updates, and additional information if relevant for study purposes. Surveys or medical chart reviews may be utilized to capture the above information throughout study participation.

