### Data analysis:

The primary analysis to compare 12-month Bayley-4 Motor scores between treatment arms, will be performed using a two-sample two-sided t-test assuming equal variance. Because the Bayley-4 scores are standardized, we expect them to follow the normal distribution. If the normality assumption is not satisfied, the Wilcoxon ranksum test will be used instead. In addition, a covariate adjusted estimate will be obtained using a linear regression model adjusted for known baseline prognostic factors, e.g. risk of neuromotor delay, gestational age at birth, and sex.

Baseline characteristics, study outcomes and treatment compliance rates will be summarized by treatment arm using basic descriptive statistics, e.g. mean, SD, median and inter-quartile range (IQR) for continuous variables, and frequencies and proportions for categorical variables.

To address questions posed in Aims 2 and 3 regarding early differences in outcomes, outcome measures will be summarized at each time point by group, and linear mixed effects models with repeated measures will be used to compare score changes over time between arms. In these models, the outcome measure, e.g., sensor data, PedsQL, GMA and others, will be the dependent variable, and predictors will include treatment arm and assessment time point as fixed effects and subject as the random effect. Within-subject correlation between repeated measurements will be accounted for by using an appropriate variance-covariance structure, e.g. autoregressive order 1 (AR(1)). Interactions between time and treatment may also be included as a fixed effect. Additional baseline prognostic covariates may also be included in the model as fixed effects to obtain covariate-adjusted estimates that may be more efficient. Differences between arms at early time points will be estimated based on the fitted model by constructing appropriate contrasts, and compared using post hoc tests. Separate models will be fitted for each outcome measure. Of note, this approach appropriately deals with missing data by including all evaluable observations across time points, rather than performing a complete case analysis. Analyses will be conducted using PROC MIXED in SAS statistical software. P-values will not be adjusted across these outcome measures because these are pre-specified analyses for outcome measures that address different aspects of the intervention.

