In addition, the dose-response relationship between the number of home visits during the 12-month period (dose) and 12-month outcomes (response) will be examined among patients randomized to the treatment arm. Data will be graphically examined using scatter plots with an overlaid lowess smoother, and linear regression models will be fitted with the 12-month outcome measure as the dependent variable, and number of visits as the predictor. Nonlinear terms may be included for the number of visits (x-variable) to model the potentially nonlinear association. These models may also be adjusted for important baseline prognostic covariates as for the primary outcome measure.

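### The dose-response regression uses a raw count of home visits, which depends on NICU discharge age, so it can show a dose effect where there is none

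*Protocol*

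**What the plan says.** The last paragraph of the protocol's Data analysis section takes the number of home visits as the dose; its subject is "the dose-response relationship between the number of home visits during the 12-month period (dose) and 12-month outcomes (response". The relationship "will be examined among patients randomized to the treatment arm", so dose is not randomised. The model is stated: "linear regression models will be fitted with the 12-month outcome measure as the dependent variable, and number of visits as the predictor". Adjustment is permissive: "These models may also be adjusted for important baseline prognostic covariates as for the primary outcome measure". The covariates listed as examples for the primary outcome are "risk of neuromotor delay, gestational age at birth, and sex". Neither discharge age nor time at home is among them.

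Three other sections determine what the count measures:
- Under Intervention Group, Block B "is defined as post-NICU until 3-months corrected age", and Block C follows it to 12 months corrected age.
- Under Procedures Involved, the Home paragraph allows up to two Block B and C sessions a week until 12 months corrected age.
- Under Block A, infants receive one or two sessions a week in the NICU before discharge.

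The additional-monitoring paragraph for the intervention group already lists "percentage of intervention sessions completed, the dosage of Activity Playbook activities achieved (caregiver report" among the items tracked. The Protected Health Information section lists NICU discharge dates among the data collected.

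**The concern.** The end of the counting window is fixed by corrected age and its start by discharge. Two infants who attend equally well can therefore have different counts only because one went home later. Length of NICU stay plausibly reflects illness: the protocol itself uses respiratory support at 36 weeks to define bronchopulmonary dysplasia and to assign the risk stratum. A long-stay infant may also have had many NICU sessions, none of which enter the dose.

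If later discharge goes with a lower 12-month Bayley-4 motor score, the slope on visit count picks up part of that prognosis and points towards benefit from more visits. Dose is one of the five principles on which the Background section rests the intervention, so a positive slope would be welcome and easily over-read. The paragraph does not warn that the association is not causal.

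**Working it through.** **Plan's own figure.** The protocol gives no figure for this analysis. The check borrows n = 77 per arm and SD 15 from the Power Analysis section. For the primary t-test these give 90.8% power (noncentral t) against the stated 90.1%, close enough to use as inputs.

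**Ceiling on the count.** Take 12 months corrected age as 40 + 52 = 92 weeks PMA. Then maximum home visits = 2 × (92 − discharge PMA):
- 36 weeks: 2 × 56 = 112
- 44 weeks: 2 × 48 = 96
- 52 weeks: 2 × 40 = 80, which is 32/112 = 29% fewer than at 36 weeks

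**Size of a spurious slope.** Let visits V = 2 × (92 − P) × A, with P the discharge PMA and A the attendance fraction. Dose has no effect. Outcome Y has SD 15 and correlation ρ with P. Assumed, not in the documents: mean P 39 weeks, mean A 0.75, A independent of outcome.

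Formula: slope = cov(V, Y) / var(V). For SD(P) = 4, ρ = −0.4 and SD(A) = 0.05:
- cov(V, Y) = 2 × 0.75 × 4 × 15 × 0.4 = 36
- var(V) = 4 × [(53² + 4²)(0.75² + 0.05²) − (53 × 0.75)²] = 64.25
- slope = 36 / 64.25 = 0.56 points per visit

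With SD(A) = 0.20, var(V) rises to 488 and the slope falls to 0.07. Simulation, with P limited to 34–56 weeks, gave 0.56 and 0.08.

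**False-positive rate.** 1,500 simulated arms of 77 per row, no true dose effect, two-sided 5% test of the dose slope. Simulation error is about 0.6 points at a 5% rate. The risk stratum was simulated from a latent variable correlated 0.6 with discharge age (assumed).

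| SD of discharge PMA (weeks) | ρ | SD of attendance (points) | Count, unadjusted | Count + risk stratum | Count + discharge PMA | Fraction attended |
|---|---|---|---|---|---|---|
| 4 | 0 | 5 | 5.7% | 4.5% | 4.1% | 4.9% |
| 4 | −0.2 | 5 | 24.3% | 16.9% | 5.5% | 5.2% |
| 4 | −0.2 | 20 | 6.8% | 5.7% | 4.4% | 5.1% |
| 4 | −0.4 | 5 | 71.8% | 54.7% | 5.3% | 4.4% |
| 4 | −0.4 | 10 | 36.6% | 27.2% | 5.3% | 5.2% |
| 4 | −0.4 | 20 | 14.2% | 10.5% | 5.9% | 6.3% |
| 2 | −0.4 | 5 | 42.3% | 25.7% | 4.9% | 6.0% |
| 2 | −0.4 | 20 | 7.6% | 7.7% | 4.7% | 4.8% |

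Over all 18 settings run, the unadjusted rate lay between 4.2% and 71.8%. The mean spurious slope was positive wherever ρ was below zero. Adjusting for risk stratum helped only in part. Adjusting for discharge PMA returned the rate to nominal.

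**If sicker infants also miss sessions.** The last two columns are near 5% only because attendance was simulated independent of prognosis. A second model set discharge age correlated 0.6 with severity, severity explaining 25% of outcome variance, attendance correlated 0.3 with severity and attendance SD 5–20 points, all assumed. The unadjusted count then gave about 49–75% false positives, the fraction attended about 14–25%, and the count adjusted for discharge PMA about 9–14%.

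**The case against.** The strongest reply is that the bias is conditional and may be small. A reader might infer that the analysis is bound to show a dose effect. The documents do not support that. They give no distribution of discharge age, no correlation of it with the Bayley-4 score and no spread of attendance. The Home paragraph expects missed sessions and scheduling around staff and families, so attendance should vary between families. With wide variation the false-positive rate drops to about 7–14% even at ρ = −0.4. This stands: the supportable word is can, not will.

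Direction is likely but not certain. Term-born infants, for example with hypoxic ischaemic encephalopathy, cannot go home before term, so they have fewer possible visits than a preterm infant discharged at 36 weeks without being sicker. The 12-month period is also undefined. If counting began at term, everyone home by 40 weeks would share a ceiling of 2 × 52 = 104.

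A reader might also infer that clinic and telemedicine sessions are left out. The protocol describes all Block B and C sessions under its Home label and then permits those settings, so the term may cover them. The omission of NICU sessions is the firmer point.

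Optional adjustment for risk and gestational age would remove some of the bias, and a statistical analysis plan, not shown, may settle the covariates. But the protocol already fixes the dose variable, and its example covariates do not include discharge age.

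Finally, replacing the count by the percentage completed changes the question: 80 of 80 and 112 of 112 become the same dose. This stands, so that measure belongs in a sensitivity analysis.

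**Conclusion.** The concern holds in conditional form. The visit count depends on discharge age by construction, adjustment is optional, and discharge age is not a named covariate. If later discharge goes with worse outcome, the regression can show a positive dose effect when there is none.

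The false-positive rate is about 5% with no such correlation and about 60–70% with a strong one and little variation in attendance. That range rests on assumed discharge ages, correlations and attendance, so no single figure within it should be quoted as the expected error.

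Severity is minor. This is a supplementary within-arm analysis, tied to none of the stated aims or endpoints, and the randomised primary comparison does not depend on it.

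**What to change.** In the dose-response paragraph of the Data analysis section:
1. Make adjustment for NICU discharge PMA (or weeks at home), risk stratum and gestational age mandatory.
2. Define the counting period, and say whether clinic and telemedicine sessions in Blocks B and C count as home visits.
3. Add a sensitivity analysis with the percentage of intervention sessions completed as dose, NICU sessions included.
4. State that the result is a non-causal association, because neither dose measure removes confounding from sessions missed through illness.

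The cost is wording only. Discharge dates and session completion are already collected. The adjusted slope will probably be weaker and less precise, since variation in visits that comes from discharge age no longer contributes. The change should be made before outcome data are examined.

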**AND**

- Medically stable **AND** able to start intervention between 34-48 weeks PMA.

*Exclusion criteria:*

(related to inability to complete intervention, sensor placement, or clinic assessments)

- open wounds, skin condition precluding sensor placement
- immune deficiencies requiring protective isolation
- limb reduction defects
- Followed primarily in another clinic (including but not limited to meningomyelocele and related conditions/trisomy 21)
- bleeding disorders or ongoing need for anticoagulation
- palliative or hospice care (for life limiting conditions including, but not limited to trisomy 18, 13)
- known visual impairment at the time of enrollment
- DCFS custody
- No English-speaking caregivers
- Any other condition that would preclude participation in the study, as determined by the PI
- Previously enrolled in competing randomized trial with developmental outcome variables

Each child’s enrollment in the study will be approved by the child’s neonatologist.

Standard of care therapists

*Inclusion Criteria:*

- Therapist treating an infant enrolled in the study post-NICU, in either the standard of care group or the intervention group.

*Exclusion Criteria:*

- ​Not treating infant involved in the study

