- Subdural, subarachnoid, or subgaleal hemorrhage with otherwise normal MRI and no seizures
- Mild abnormalities on cranial ultrasound or MRI (including, but not limited to, non-cystic periventricular leukomalacia (PVL) or mild white matter injury)
- BW<1500 grams with grade 0, 1 or 2 intraventricular hemorrhage (IVH)
- No BPD or Jensen Grade 1 nasal cannula (NC) ≤ 2 liters per minute LPM) at 36 weeks

*Moderate-Severe risk:*

- Clinical HIE diagnosis or meningitis with abnormal MRI OR seizures
- Grade III/IV hemorrhage
- Cystic PVL
- Ventriculoperitoneal (VP) shunt
- Stroke
- Cramped synchronous movements
- BPD (respiratory support > 2 LPM NC at 36 weeks)
- Brain developmental abnormalities (hydrocephalus, microcephaly, cortical dysgenesis)
- Other surgical or medical condition likely to increase risk of neuromotor delay based on clinical judgement, at the discretion of the PI

*Intervention:*

*NICU:* The NICU intervention sessions (approximately 40 minutes to one hour) will be provided 1-2 times per week, based on caregiver needs and infant tolerance. Intervention sessions will be scheduled after completion of baseline assessment until discharge from the NICU. Intervention therapists may work with project coordinators, allied health professionals, and caregivers for appropriate timing of the intervention sessions. An attempt to reschedule any missed sessions will be made. At the beginning of each session, intervention therapists will review any changes in infant status/state with caregivers and/or allied health professionals. They will work collaboratively with caregivers to identify the infant’s current state of arousal, monitor for significant and consistent stress signals during the session, and modify activity selection based on infant tolerance. Staff will record session outcomes and complete appropriate forms in REDCap. For infants that may require additional support during intervention sessions (infants who require respiratory support >2 LPM nasal cannula and others based on bedside nurse recommendation) a research nurse will attend the intervention or assessment to monitor the infant.

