*Home:* The Block B and C intervention sessions will be provided up to 2 times per week, until 12-months corrected age. Intervention sessions will be scheduled based on staffing and caregiver/infant schedules. Session attendance will be monitored and any missed sessions will be rescheduled if possible. Due to the length of the study, it is possible that infants may miss some intervention sessions. Intervention therapists will complete a subjective caregiver survey at the initiation of each session and will appropriately record session outcomes and update appropriate forms in REDCap.

*Activity Playbook*: In addition to the therapist-provided intervention sessions outlined above, caregivers will be provided with an Activity Playbook comprising video and written resources for activities. Completion of these activities will be tracked. If needed, the monitoring mode will be adjusted to fit the needs of the caregiver (e.g., myCap, paper log, phone call). As applicable, intervention therapists will assist in identifying strategies to address any challenges that caregivers may be facing in completing the activities or in achieving or progressing the target dose.

*Toy Kits*: We will provide developmentally appropriate toys to families in the intervention group periodically throughout the intervention phase, to enable families to provide environmental enrichment irrespective of family resources*.* Children in the standard of care group will receive developmentally appropriate toys at the end of their participation in the study, so that each child receives a similar number of toys over the course of the study.

*Mode of Intervention Sessions*: The primary method for intervention delivery will be in-person sessions at the participant’s home or NICU. However, based on the needs of the individual family or infant, sessions may be provided in-clinic (for those in Blocks B or C) or virtually (Blocks A, B, and C); this flexibility will maximize intervention dosage. If sessions are provided in the clinic, families will be reimbursed for parking expenses. Families will be screened for COVID-19 prior to each intervention session. If any member of the family is unwell or there is a known exposure to COVID-19, the session will be rescheduled or conducted via telemedicine.

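### The dose-response regression uses a raw home-visit count that partly reflects age at NICU discharge, so its slope can be biased towards a positive dose effect

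*Protocol*

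**What the plan says.** The Data analysis section of the protocol defines dose as the number of home visits and restricts the analysis to infants randomised to the intervention: "the dose-response relationship between the number of home visits during the 12-month period (dose) and 12-month outcomes (response) will be examined" in that arm. It states that "linear regression models will be fitted with the 12-month outcome measure as the dependent variable, and number of visits as the predictor". Scatter plots with a lowess curve and optional nonlinear terms accompany the model. On adjustment it says only: "These models may also be adjusted for important baseline prognostic covariates as for the primary outcome measure". The primary-outcome model to which this refers is "adjusted for known baseline prognostic factors, e.g. risk of neuromotor delay, gestational age at birth, and sex".

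The window for home visits is fixed elsewhere. Under Intervention Group, Block B "is defined as post-NICU until 3-months corrected age", and Block C follows it. Under Procedures Involved, "The Block B and C intervention sessions will be provided up to 2 times per week, until 12-months corrected age". Sessions before discharge form Block A; they "will be provided 1-2 times per week, based on caregiver needs and infant tolerance" and are not home visits. Eligible infants must be "able to start intervention between 34-48 weeks PMA". The Consent Process section also allows consent after discharge, up to about 48 weeks PMA.

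**The concern.** The home-visit window has an infant-specific start and a common end, so the 12-month period in the dose definition does not have the same length for every infant. Two infants with identical attendance can have different doses only because one went home later. If late discharge also marks worse motor prognosis, a regression of the 12-month score on the raw count attributes part of that prognosis to the visits. The bias runs in one direction, towards more visits appearing to give better scores.

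The protocol gives some support for a link with prognosis. It treats respiratory support at 36 weeks PMA as a risk marker, and it pauses the intervention for surgery. It gives no figure for the strength of the link.

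The planned safeguard is optional and limited to baseline covariates. Discharge age arises after enrolment and is not named. Dose is one of the five principles on which the intervention rests (Background), so a positive slope would be read as support for it.

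**Working it through.** The protocol states no figure for this analysis, so there is none to reproduce. Its own inputs are 77 infants per arm and SD 15 (Power Analysis), two visits a week at most, and a window from discharge to 12 months corrected age. Taking term as 40 weeks and a year as 52 weeks, 12 months corrected age is 92 weeks PMA.

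**Ceiling on the count.** Maximum home visits = 2 x (92 - discharge PMA in weeks).

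| Discharge PMA (weeks) | Window (weeks) | Maximum home visits |
|---|---|---|
| 36 | 56 | 112 |
| 40 | 52 | 104 |
| 44 | 48 | 96 |
| 48 | 44 | 88 |

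Discharge at 48 rather than 36 weeks removes 112 - 88 = 24 possible visits, or 24/112 = 21%. Over those 12 weeks an infant already enrolled could receive 12 to 24 neonatal-unit sessions (1-2 a week), none of which enters the count.

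**Comparison with attendance.** At discharge week 40, attendance of 90% gives 0.90 x 104 = 94 visits and attendance of 60% gives 0.60 x 104 = 62, a gap of about 31. Ordinary variation in attendance can therefore move the count as much as discharge age does.

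**Effect on the slope.** I simulated 77 infants with a true visit effect of zero and regressed the score on the raw count (3,000 runs per setting). The following are assumptions, not figures from the protocol: discharge PMA normal with mean 40 and SD 4 weeks, truncated to 35-53; mean attendance 0.75, unrelated to severity; Bayley-4 falling 1 or 0.5 points per week of later discharge; total SD about 15.

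| Attendance SD | Visit variance explained by discharge age | False positives, 1 point/week | False positives, 0.5 points/week |
|---|---|---|---|
| 0.05 | 49% | 28% | 11% |
| 0.10 | 20% | 14% | 7% |
| 0.15 | 10% | 10% | 6% |
| 0.20 | 7% | 7% | 6% |

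The nominal rate is 5%. At 1 point per week the mean spurious slope falls from 6.6 to 0.8 Bayley points per 20 visits as attendance SD rises from 0.05 to 0.20.

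Stronger assumptions give more: with a correlation of 0.3-0.5 in size between discharge age and score, discharge SD 3-5 weeks and attendance SD 0.03-0.20, the rate spans 9-98%. The top of that span needs almost uniform attendance.

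**Remedies, same simulation.**
- Adding a two-level risk stratum related to discharge age leaves about 22% at 1 point per week and attendance SD 0.05. It reduces the bias without removing it.
- Adding discharge PMA to the visit-count model gives about 4-6% in every setting.
- Replacing the count by the share of available sessions gives about 5% if attendance is unrelated to severity. If attendance falls 1 percentage point per week of later discharge, the share alone gives up to 19%, while the visit count with discharge PMA stays at about 5%.

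The simulation lets severity act only through discharge PMA, so it shows the best that this covariate can do. Adjustment for gestational age was not simulated.

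**The case against.** The analysis is supplementary, has no hypothesis, alpha or power claim, and is described as an examination of an association. The covariate list is open, given as examples. It includes the risk stratum, which contains conditions likely to delay discharge, and gestational age. A statistical analysis plan that is not shown may settle the final covariates.

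Discharge PMA is also an imperfect marker of severity in this population. An infant born near term with hypoxic ischaemic encephalopathy and a normal MRI cannot go home at 36 weeks, however well, whereas a low-risk infant under 1500 g can. A straight line from later discharge to worse outcome ignores that mix.

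Most of this stands, and it limits the point. It does not answer it: the protocol itself fixes the dose variable as a raw count and confines the adjustment to optional baseline covariates. That is a choice already made, not a detail left open.

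A reader might infer that discharge age mainly determines the count, or that a false dose effect will appear. The documents support neither. They give no distribution of discharge age or attendance, they expect missed sessions and scheduling limits, and at attendance SD 0.10-0.20 discharge age explains only 7-20% of the variation. Even at a 28% false-positive rate most trials would show no significant slope.

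A reader might also think that dividing by available sessions cures the problem. That ratio measures adherence: 88 of 88 and 112 of 112 both equal 1. A denominator counted from discharge would also charge infants consented after discharge with weeks before they enrolled.

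**Conclusion.** The point holds in a limited form. The raw visit count mixes the length of the available window with attendance, and the planned model need not separate them. Following the text as written can bias the slope towards a positive dose effect if later discharge goes with worse prognosis.

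The ceiling arithmetic follows from the protocol and the 40-week convention. The false-positive rates of about 7-28% and 6-11% rest on the assumed discharge spread, attendance spread and outcome gradient, and range from negligible to material. The primary comparison, its power and its type I error are unaffected.

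**What to change.** In the dose-response paragraph of Data analysis, keep the number of home visits as the dose. State that the model always includes PMA at the start of home visits (NICU discharge, or enrolment if consent came after discharge), risk stratum and gestational age at birth. State that the slope will be reported as a non-randomised association, since confounding by severity that these covariates do not capture would remain. The share of available sessions may be added as a sensitivity analysis of adherence, counted from the same start date, but not as a replacement for dose.

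The cost is about two sentences. Discharge dates and session attendance are already collected. The slope will be somewhat less precise, because part of the variation in visit count is given up to the covariates.
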